#### Approach bias re-training

Alcohol automatic approach tendencies are assessed and trained with the Approach-Avoidance Task (AAT) [14,15,20,28], which is a computerised speeded reaction-time task in which participants are asked to react to the presentation format of the stimulus and ignore the stimulus content (irrelevant-feature implicit measure [30]).

In this task, a picture of an alcoholic or non-alcoholic drink is presented in the centre of the screen. The picture is tilted to the left or right by three degrees. Participants are instructed to respond to the tilt direction of the picture by pushing pictures tilted to the left away from them, and pulling pictures tilted to the right towards them, by pressing and holding two keys (U and N) on the keyboard. The combination of picture tilt direction and response (left/push and right/pull versus left/pull and right/push) is counterbalanced across participants. Participants’ response is accompanied by a zooming effect, which increases picture size in the pulling closer response and decreases it in the pushing away response, mimicking actual approach and avoidance (for an example of a trial, see Figure 2).

In the AAT assessment version and in the mini-assessment block during training, pictures of alcoholics and non-alcoholics are presented equally often in both formats. The approach bias score is computed following the conventional D-score algorithm generally used in the Implicit Association Test [35], and adapted by Wiers *et al*. to the AAT [18], which standardises the difference in RTs by dividing the difference by the individual standard deviation (SD) of RTs. An approach bias D-score is computed for alcohol ((alcohol/push − alcohol/pull)/SD(alcohol)) and for non-alcohol trials ((non-alcohol/push − non-alcohol/pull)/SD/non-alcohol)). Positive scores indicate an approach tendency, negative ones indicate an avoidance tendency.

In the training block, participants in the experimental condition are trained to avoid alcohol by exposing them only to alcohol/push and non-alcohol/pull trials, whereas for participants in the placebo condition alcoholic and non-alcoholic beverages are presented equally often in both formats (as in the AAT assessment version and in the mini-assessment blocks).

Stimuli are pairs of matched alcohol and non-alcohol pictures, which are counterbalanced for presentation format only for assessment. Stimuli stay on screen for 3,000 ms; in cases of no response the trial is restarted after repeating the instructions.

#### Tasks stimuli

The current beverage picture set is an Italian adoption of the Amsterdam Beverage Picture Set (ABPS; Pronk T, Van Deursen DS, Beraha EM, Larsen H, Wiers RW. Validation of the Amsterdam Beverage Picture Set: a controlled picture set for cognitive bias measurement and modification paradigms. Forthcoming). As such, half of the pictures are passive pictures that display beverages in front of a white background, the other half being active pictures that display beverages being held, opened, drunk or served by a model in front of a white background. Prior research indicated that for heavy drinkers, alcohol displayed in a social setting induced stronger self-reported craving [36] and stronger emotional responses [37] than alcohol in front of a white background. This may be due to alcohol in a social setting being a more naturalistic cue than the alcohol without any context. In contrast, pictures without context did induce a stronger attentional bias [38] than social pictures. This may be due to fast mental processes such as cognitive biases being most effectively triggered by simple stimuli that solely feature a stand-alone alcoholic or non-alcoholic beverage. The pictures used in the current study were designed to be relatively simple, but nevertheless feature beverages both with (active) and without (passive) drinking contexts. This distinction is aimed at keeping pictures relatively simple, while allowing for a sufficiently varied stimulus set.

The stimulus set features 144 pairs of alcohol and non-alcohol pictures matched by structural, visual and pictorial features and photographed in both passive (beverage only) and active (presence of a human in interaction with the drink) contexts. Alcohol pictures depict highly popular and recognisable Italian brands of wine, beer and spirits. A common non-alcoholic drink was selected for each alcoholic beverage by matching, as much as possible, the type of packaging (bottle, can, jar or carton), package size and colour.

Drinks were then photographed in a neutral setting (windowless room with a table on a white background, full illumination on the centre of the table, various glasses for the different drinks, a tray and a bottle opener) and according to the following criteria: drinks in the foreground of the picture, consistent framing to shoot pictures from the same angle and use of a standard digital camera.

Drinks were photographed in six scenarios, three for each context (passive: open beverage only, open beverage with empty glass and open beverage with full glass; active: woman serving the open drink on a tray, woman or man opening the drink and woman or man drinking). In woman or man active scenarios, alcoholic drinks, as well as their matched non-alcoholic drinks, were counterbalanced for drink category (wine, beer and spirits) and gender; whereas in the three passive scenarios each picture was shot in each scenario.

Stimuli were processed in Adobe Photoshop CS6 (Adobe Systems Incorporated, San Jose, California, USA) to adjust for size, exposure, brightness, contrast and to correct minor image imperfections (see Additional file 1: Table S1 for some examples of stimuli). Stimuli are randomised with 50/50 proportion of passive and active pictures in each task. In each training session untrained and already trained pictures are presented. At the pre- and post-intervention assessment session the VPT and AAT use different untrained stimuli. The follow-up measurement session is equal to the post-intervention session; the same stimuli are used.

### Measures

An overview of all measurement instruments along the RCT measurement time-points is presented in Table 1.

**Table 1 Tab1:** **Measurement instruments: purpose, measures and time points**

**Purpose**	**Measures**	**Baseline**	**Training**	**Post-intervention**	**Follow-up**
Cognitive bias assessment	VPT AAT	✓	✓	✓	✓
Generalisation of training effects	BIAT	✓		✓	
Executive function	Stroop task	✓		✓	
Baseline measures	Demographics Case history details RSES	✓			
Primary outcome measure	Clinical status (lapse/relapse)	✓		✓	✓
Secondary outcome measures	AUDIT^a^ CORE Alcohol/Drug use^a^ OCDS STAI-Y BDI-II	✓		✓	✓
Motivation to treatment	MAC2-A	✓		✓	
	Motivation to training		✓		

^a^At baseline, post-intervention and follow-up measurement sessions, the questionnaire refers to the last 12, 1, and 3 months, respectively.

VPT: Visual Probe Task; AAT: Approach-Avoidance Task, BIAT: Brief Implicit Association Task, RSES: Rosenberg Self-esteem Scale, AUDIT: Alcohol Use Disorder Identification Test, OCDS: Obsessive-Compulsive Drinking Scale, STAI-Y: State-Trait Anxiety Inventory – Form Y, BDI-II: Beck Depression Inventory-II, MAC2-A: Motivation to Change-Alcohol version.

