## Methods/Design

### Trial design

The present study is a phase II, double-blind, parallel group RCT. Following the design of previous CBM studies [18,19], participants complete 11 sessions of either the active or placebo version of both attentional and approach bias training modules. The experimental intervention has a 2×2 factorial design, which combines the active and placebo training modules into four experimental conditions: one double active training experimental condition, two experimental groups receiving one active training and one placebo training and one double placebo training control group. According to the experimental design, the probability of receiving at least one active CBM intervention reaches 75%. The placebo version of each training module consists of a continuous assessment, in which half of the trials train the cognitive biases away towards alcohol and the other half towards soda (active placebo). The manipulation of the stimulus-response contingency in each task allows for a controlled and clean comparison between experimental conditions while retaining the same tasks, stimuli and instructions. Also, Wiers *et al*. [18] found no differences between continuous assessment and no-training placebo conditions, which suggested that either type of placebo could be used.

Participants complete a total of 14 sessions: two baseline assessment sessions, 11 training sessions, one post-intervention assessment session and one three-month follow-up assessment session. Participants complete the training sessions with a between-session time interval of a maximum of five days. The post-intervention assessment takes place between the 10th and 11th training session during a ‘masked’ session (participants do not know they are completing the post-intervention evaluation). That is to avoid possible negative feelings related to the final ‘evaluation’ of the intervention and minimise self-presentation biases and/or preparatory strategies.

Participant flowchart as per Consolidated Standards of Reporting Trials (CONSORT) statement [27] is presented in Figure 1. The study was approved by the Ethics Committee of the School of Psychology of the University of Padova (March 2013; Protocol number: 1242) and registered at Current Control Trials (identifier: ISRCTN01005959).

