**Participant flow diagram.**

### Participants and procedure

Participants are adult outpatients with a main diagnosis of alcohol addiction disorder, recruited from the public health addiction service (Servizio per le Dipendenze, ULSS10) of San Donà di Piave, Italy. The targeted number of recruited participants is 120, to be equally balanced across the four experimental conditions.

Participants are screened for eligibility according to the following criteria:Inclusion criteria: adult outpatients with primary diagnosis of alcohol addiction disorder according to the diagnostic criteria of the Diagnostic and Statistical Manual of Mental Disorders (4th Edition, Text Revision) and alcohol abstinence for at least two months.Exclusion criteria: neurocognitive problems, visual or hand-motoric handicaps, severe neurological disorders (such as Korsakoff syndrome), comorbidity with psychotic disorders or low fluency in the Italian language.

Participants are recruited by clinicians according to the inclusion and exclusion criteria and invited to participate in the study. At invitation, clinicians provide the patients with a brief introduction to the study by explaining that addiction disorders are partly due to uncontrolled and automatic processes which can substantially increase the risk for relapse, and that the main objective of the research is to test the effectiveness of new computerised treatment interventions, which can help the patient in gaining and increasing a better control over these underlying mechanisms. The clinician will also supervise patients’ activity and progress along both the patient’s standard treatment and the experimental intervention.

After the patients are informed about the research objectives and the norms for confidential data treatment and for participating in the study, interested participants undersign a written informed consent form and create their research account at the training website.

Participants will be excluded from the study if they do not complete the baseline assessment or if they disclose the intention to discontinue the study. All participants will continue their treatment as usual in the public addiction service. Upon completion of the three-month follow-up assessment, they have the opportunity to attend the double active CBM training if they wish. The percentage of participants that enter the booster training is registered.

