### Outcome measures

The main outcome measure is the occurrence or not of lapse and/or relapse episode(s) during the three months after the intervention (follow-up assessment). The treatment status (any medication intake and other form of therapeutic intervention) at the follow-up assessment is also considered in comparison to the baseline status.

Secondary outcome measures include changes in the automatic cognitive biases as assessed with the VPT and AAT at post-intervention and follow-up assessment sessions. At the follow-up assessment, VPT and AAT present the same stimuli of the post-intervention session, to check for the duration of the training effects.

Generalisation effects of the two CBM modules to other measures are assessed at post-intervention with the BIAT [20-22]. Other secondary outcome measures (assessed at each measurement point) also include other substance abuse (CORE questionnaire), alcohol-related problems (AUDIT), craving (OCDS), anxiety (STAI-Y), depression symptoms (BDI-II) and motivation to treatment (MAC2-A; measured at pre- and post-intervention only).

Intervention credibility and expectancies are also assessed with the Credibility/Expectancy Questionnaire [50] to evaluate participants’ general experience with the study.

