### Data analysis

Complete analyses will be conducted in agreement with Intention-To-Treat principle [26]. Missing data points will be handled with multiple imputation.

To answer to the main research question, a multiple logistic regression will be used to estimate how much the main and combined exposure to the two CBM modules affects the occurrence of lapse and/or relapse episodes at the three-month follow-up assessment.

The secondary research question, whether participants approach and attentional biases do change after the CBM intervention, is addressed via a 3×2×3 repeated-measures mixed ANOVA with the AAT and VPT scores as dependent variables, time (baseline, post-intervention and follow-up) as repeated measures within-subject factor, drink type (alcoholic and non-alcoholic) or attentional process (engagement and disengagement) as within-subject factor, and CBM condition (re-training or placebo) as between-subject factor. The same analysis applies to the continuous secondary outcome measures administered at each time point.

The third research question of the present study is framed within a ‘what works best for whom?’ approach [8] and explores the moderating and mediating roles of individual differences variables on the clinical outcome by means of a moderated mediation analysis [51]. More precisely, baseline strength of the cognitive biases and interference control capacity (Stroop task), as well as age, gender and previous detoxifications, are hypothesised to moderate the change in cognitive bias after the CBM intervention, which is further hypothesised to eventually mediate the change in the clinical outcome variable (see Eberl *et al*. [19]).

Finally, participants’ motivation to change (MAC2-A) at pre- and post-intervention will be compared via a paired t-test. Via a repeated-measures ANOVAs we will explore whether change in participants’ motivation to carry on with the training after the brief MS interviews affects attrition and training outcome.

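### AUDIT (and CORE, if scored continuously) is recalled over 12, 1 and 3 months but analysed on one time factor, so change over time is confounded with recall window; the arm comparison is not biased

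*Protocol article*

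**What the plan says.** In the Protocol article, Table 1 lists the secondary clinical measures as "AUDIT^a^ CORE Alcohol/Drug use^a^ OCDS STAI-Y BDI-II". The footnote mark stands on AUDIT and CORE only, and the footnote reads "At baseline, post-intervention and follow-up measurement sessions, the questionnaire refers to the last 12, 1, and 3 months, respectively". OCDS, STAI-Y and BDI-II carry no such mark.

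The Outcome measures section names both AUDIT and CORE as secondary outcomes taken at every measurement point. The abstract counts change in the clinical variables among the secondary outcomes.

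The Data analysis section specifies a mixed ANOVA for the bias scores with "time (baseline, post-intervention and follow-up) as repeated measures within-subject factor" and "CBM condition (re-training or placebo) as between-subject factor". It then adds: "The same analysis applies to the continuous secondary outcome measures administered at each time point". It mentions no common recall window, no per-month rescaling and no baseline covariate.

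Eligibility (Participants and procedure) requires "alcohol abstinence for at least two months".

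**The concern.** A repeated-measures time factor presumes that the same quantity is measured at each level. Here the three AUDIT scores describe periods of 12, 1 and 3 months. If a longer period gives more opportunity to report drinking or its consequences, the score can fall from baseline to post-intervention and rise again at follow-up with no change in behaviour.

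The eligibility rule sharpens this. The 12-month baseline window can hold up to about 10 months (12 − 2) from before the required abstinence. In the last month before baseline, by contrast, drinking should be nil by eligibility. Measured over one month throughout, drinking could only stay level or worsen; measured as planned, the same patients can appear to improve.

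Change is a declared secondary outcome, so a time effect or within-arm change on AUDIT could be reported as a clinical result when part or all of it comes from the questionnaire's time frame.

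**Working it through.** **Plan's own figure.** There is none on this point. The only power figure in the article, the minimal detectable odds ratio of 0.396, belongs to the primary outcome and does not enter here.

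**Step 1: window length alone.** Inputs: windows of 12, 1 and 3 months (Table 1 footnote) and a constant monthly event chance p (assumed; the article gives none). The share reporting at least one event in w months is 1 − (1 − p)^w.

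| p (assumed) | 12 months (baseline) | 1 month (post-intervention) | 3 months (follow-up) |
|---|---|---|---|
| 0.05 | 1 − 0.95^12 = 46% | 5% | 1 − 0.95^3 = 14% |
| 0.10 | 1 − 0.90^12 = 72% | 10% | 1 − 0.90^3 = 27% |
| 0.20 | 1 − 0.80^12 = 93% | 20% | 1 − 0.80^3 = 49% |

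Nothing changes in truth, yet every row shows a fall and then a rise.

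**Step 2: does this bias the arm comparison?** Randomisation gives the arms the same expected baseline score, whatever its window. Hence E(follow-up − baseline | active) − E(follow-up − baseline | placebo) = E(follow-up | active) − E(follow-up | placebo). The window effect cancels.

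A simulation agrees. Inputs, all assumed except the group sizes: 60 against 60 for one module, a stable personal monthly rate from a gamma distribution (shape 2, scale 0.25, mean 0.5), Poisson counts over 12 and 3 months, and two-sided 5% tests. With no change and no treatment effect (4,000 runs):

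- baseline-to-follow-up change was significant in 100% of runs, with mean −4.5 = 0.5 × (3 − 12);
- the arm comparison of change was significant in 5.1%;
- the baseline-adjusted arm comparison was significant in 5.4%.

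**Step 3: what the arm comparison loses.** In the same model the rate has variance 2 × 0.25² = 0.125.

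- Var(12-month count) = 6 + 144 × 0.125 = 24
- Var(3-month count) = 1.5 + 9 × 0.125 = 2.625
- Covariance = 36 × 0.125 = 4.5
- Variance of the change: 24 + 2.625 − 2 × 4.5 = 17.625
- Residual variance after baseline adjustment: 2.625 − 4.5²/24 = 1.781

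Subtracting the 12-month score therefore gives about 9.9 times the variance of adjusting for it. Simulated power (3,000 runs each) was 11% for change against 80% with baseline as covariate at an assumed rate ratio of 0.6, and 9% against 51% at 0.7. These figures illustrate the mechanism for two visits of a count outcome. They are not estimates for AUDIT, nor for the full three-level ANOVA.

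**Step 4: outcomes without the footnote (VPT, AAT, OCDS, STAI-Y, BDI-II).** With equal variances and baseline–outcome correlation r (assumed), the variance of a simple change-score comparison relative to baseline adjustment is 2(1 − r)/(1 − r²) = 2/(1 + r): 1.54 at r = 0.3 and 1.33 at r = 0.5. This is a matter of efficiency only.

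**The case against.** The strongest reply is that the trial's hypotheses compare active with placebo training, and all arms answer the same questions over the same windows. That stands. A reader might infer from the mismatch that the treatment test on AUDIT is invalid, but Step 2 shows that it is not: the randomised comparison keeps its level and its target, and only loses precision.

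A reader might also infer that the repeated-measures ANOVA is wrong for every continuous outcome and that baseline must always be a covariate. The article does not support this. The footnote covers two instruments, and for the others the ANOVA is a valid test of condition by time.

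Three further objections hold in part.

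- The article does not describe AUDIT or CORE scoring, and a constant event rate is unrealistic in patients selected for abstinence. The percentages therefore show direction and plausibility, not the size of the artefact.
- CORE's place in the ANOVA is inferred, since the article restricts that analysis to continuous measures and gives no CORE score. AUDIT is the clearer case.
- The shorter later windows are disclosed and sensible. Eleven sessions with a "between-session time interval of a maximum of five days" span at most 10 × 5 = 50 days, so a 12-month window at post-intervention or follow-up would overlap the baseline period. This justifies the windows, but not treating the three scores as one repeated measure.

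**Conclusion.** The point holds for AUDIT, and for CORE if it is scored continuously. The stated analysis does not fit the stated measurement schedule: the time main effect and within-arm change are confounded with recall window, and the 12-month baseline normally includes drinking from before the required abstinence. Nothing in the article allows the artefact to be sized. Under assumed constant monthly chances of 5% to 20%, window length alone would move the share reporting any event from 46–93% at baseline to 5–20% and then to 14–49%.

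The arm comparison is unbiased but noisier than it need be; how much noisier depends on assumptions that the article does not settle. The consequence is modest, because only secondary outcomes are involved and the primary logistic regression on lapse or relapse is unaffected.

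**What to change.** For AUDIT and any continuous CORE score, replace the three-level time factor with two separate arm comparisons, one at post-intervention and one at follow-up. Each should have terms for the two training modules and the 12-month baseline score as covariate. Keeping the visits separate also deals with the remaining mismatch between the 1-month and 3-month windows, which a baseline covariate alone would leave in place. State that the time main effect and within-arm change will not be interpreted for these instruments, and say whether CORE gives a continuous score.

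Optionally, and as an efficiency gain rather than a correction, use baseline as a covariate instead of an outcome level for VPT, AAT, OCDS, STAI-Y and BDI-II.

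The cost is analysis wording only: all the scores needed are already scheduled, and no assessment, sample size or visit changes.

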### Baseline measures

Sociodemographic information (gender, birthdate, annual income and educational level) and clinical case history details (duration of alcohol addiction, previous detoxifications and treatments, duration of current abstinence and medication intake) are collected during participants’ research registration.

At the first baseline assessment session, other substance use (integration of CORE Alcohol and Drug Abuse Survey (CORE Institute) and the Italian Population Survey on Alcohol and other Drugs questionnaire (National observatory for Drug Use)), self-esteem (Rosenberg Self-Esteem Scale, RSES) [39,40], anxiety (State-Trait Anxiety Inventory-Y, STAI-Y) [41] and depressive symptoms (Beck Depression Inventory-II, BDI-II) [42] are evaluated. After the questionnaires, participants are assessed for baseline alcohol approach bias (VPT) and attentional bias (AAT).

At the second baseline assessment session, alcohol abuse (Alcohol Use Disorders Identification Test (AUDIT)) [43], craving (Obsessive-Compulsive Drinking Scale, OCDS) [44] and motivation to treatment (MAC2-A) [33] are evaluated.

After the questionnaires, a computerised version of the classical Stroop task [45,46] is used to assess interference control capacity [18,19,26]. In this task, participants have to classify words and symbols according to their ink colour and ignore the content. The task starts with a practice block, in which participants have to learn the correct key-colour combination (only neutral and incongruent trials are presented). The second block consists of a second practice block task with grey key reminders on the bottom of the screen. The third block is a test block composed of 112 trials in which the key reminders disappear and 16 neutral trials (such as symbols like #### in blue ink colour), 48 congruent trials (such as the word ‘red’ in red ink colour) and 48 incongruent trials (such as the word ‘red’ in yellow ink colour) are presented.

The second assessment session ends with a Brief Implicit Association Task (BIAT) [47] measuring the strength of approach and avoidance associations with alcohol [18,19]. In the BIAT, participants are required to choose whether word stimuli presented in the centre of the screen belongs to one of two focal categories on top of the screen or not, by pressing the ‘yes’ and ‘no’ corresponding keys (E and I). In the first block (16 trials) participants practice the task by classifying words for alcoholic beverages (wine, beer, vodka and rum), non-alcoholic beverages (pepsi, milk, water and tea), mammals (horse, sheep, cat and elephant) and birds (swallow, eagle, hawk and pigeon), as belonging to alcohol or mammals (focal categories) or not (‘anything else’ category). In the subsequent four blocks (20 trials each), the alcohol focal category is alternatively paired with approach (block two and four) or avoid (block three and five) attribute category. Test attribute stimuli for approach (grab, approach, closeness and touch) and avoidance (flee, push, avoidance and elude) have been adapted from Wiers *et al*. [18] and Ostafin and Palfai [48]. The order of the combined blocks for the alcohol/[attribute category] pairings within the BIAT and the contingency between the response and the assigned key (E and I) are counterbalanced across participants. The outcome measure is computed as the standardised difference in latencies between the different combined blocks (modified D-score algorithm [49]). As a control measure, participants subsequently rated BIAT stimuli on valence with a visual analogue scale from 0 (extremely negative) to 10 (extremely positive).

